#### Specific Aim 2: Do Modifiable Factors Predict Short- and Long-Term Changes in Ambulatory Measures of Cognitive Functioning?

##### Short Term

Mixed effects multilevel models (MLMs) for momentary (within-day) associations, one for each ambulatory cognitive variable (perceived cognitive function and cognitive test scores), will be constructed. In each case, predictor variables of interest will be physical activity (accelerometer data), sleep (accelerometer data and EMA-sleep quality), and EMA measures of fatigue, pain, mood, and stress from the previous within-day time point (all moment-to-moment analyses will be conducted within-day). Similarly, MLMs for day-level associations, one for each cognitive variable, will be constructed; only day-level analyses will explore the association between sleep and cognition. Given the lack of data on the temporal effects of these variables on cognitive functioning, exploratory analyses of lagged effects (1- and 2-day lag) will also be examined.

##### Long Term

Ambulatory measures of predictor and outcome variables will be aggregated within a time period for baseline and 1- and 2-year follow-up periods. Laboratory-based measures of cognitive functioning will also be examined. MLMs will be used to test whether ambulatory measures of physical activity, sleep, fatigue, pain, mood, and stress predict changes in objective or subjective measures of cognitive functioning (ambulatory and laboratory-based measures) 1 or 2 years later. The change will be modeled within an analysis of covariance framework, where T2/T3 values for an outcome of interest are modeled controlling for T1 values of the said outcome. In contrast to specific aim 1, where the primary interest is on comparing the performance of the ambulatory tests to standard clinic-based cognitive tests, the primary interest of specific aim 2 is in understanding what factors contribute to variation or changes in cognitive function and in identifying probable targets for cognitive rehabilitation regardless of the measure used to identify such associations; therefore, no direct comparisons between measurement types will be made.

#### Specific Aim 3: Do Ambulatory Measures of Cognitive Functioning Predict Social and Physical Functioning Over Short-Term and Long-Term Time Frames?

##### Short Term

In the momentary data, MLMs will be constructed to predict same-day social participation and physical functioning (upper- or lower-extremity functioning, balance, and falls or missteps) from the ambulatory cognitive variables. Analyses for falls or near falls will be conducted using a special case of MLM for categorical outcomes. Exploratory analyses of lagged effects (1- and 2-day lag) will also be examined.

##### Long Term

In terms of distal prediction of social and physical function from ambulatory cognition, we will conduct MLMs with the cognitive variables (averaged across each time period) predicting social and physical functioning at 1- and 2-year follow-up. The change will be modeled within an analysis of covariance framework, where T2/T3 values for an outcome of interest are modeled controlling for T1 values of the said outcome. These MLMs exploring long-term associations between cognitive changes and changes in social and physical functioning will be repeated in a set of secondary analyses with standard clinic-based cognitive test scores as predictor variables. Prediction of long-term changes in social and physical functioning from ambulatory cognitive measures will be compared to the ability of laboratory-based measures to predict these same changes. Ambulatory measures of cognition are of primary interest for specific aim 3, given that their microlongitudinal burst design allows for examination of short- and long-term associations, and are assumed to be more reliable and therefore more likely to demonstrate robust associations with the other functional outcomes.

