### CogDetect-MS Study Measures: Laboratory Visit Measures

#### Self-Report Measures

The self-report survey battery includes surveys of demographics, clinical characteristics, and medical history (eg, medications and therapies) and a selection of valid and reliable self-report measures (Table 1 and Multimedia Appendix 1).

**Table 1 table1:** Validated self-report surveys administered in the Optimizing Detection and Prediction of Cognitive Function in Multiple Sclerosis (CogDetect-MS) study.

Domain	Measures
Sleep	PROMIS^a^ Sleep Disturbance Short Form 8b [36] STOP-Bang [37]
Fatigue	PROMIS Fatigue Short Form 8 V1.0 [38] Michigan Fatigability Index Short Forms
Pain	PROMIS Pain Intensity 3a [36] PROMIS Pain Interference 8a [39-41] painDETECT [42] American College of Rheumatology Fibromyalgia Diagnostic Criteria [43,44]
Depressed mood	PROMIS Depression 8b [45]
Stress	Perceived Stress Scale [46]
Social functioning	Neuro-QoL Ability to Participate in Social Roles and Activities Short Form 8 [47,48]
Cognitive function	PROMIS Cognitive Abilities Short Form 8 [49] Compensatory Cognitive Strategies Scale [50]
Physical functioning	Neuro-QoL Upper Extremity Function-8 [47] Neuro-QoL Lower Extremity Function-8 [47] Patient Determined Disease Steps [51]
Falls	1-Month Falls History Falls Efficacy Scale [52] Fear of Falling Avoidance Behavior Questionnaire [53] Concern and Fear of Falling Evaluation [54,55]
Substance use	Tobacco, Alcohol, Prescription Medications, and Other Substances Tool [56-58]
Comorbidities	Comorbidity Questionnaire [59]
Personality^b^	Ten-Item Personality Inventory [60]
Demographic and clinical variables	Demographic and clinical characteristics survey Pet ownership survey [61]

^a^PROMIS: Patient Reported Outcomes Measurement Information System.

^b^Evaluated at T1 visit only.

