**Ecological momentary assessment (via smartphone app)**			
	Perceived cognitive function (3 items)	4× per day	
	Pain intensity (1 item)	4× per day	
	Fatigue intensity (2 items)	4× per day	
	Perceived stress (1 item)	4× per day	
	Depressed mood (3 items)	4× per day	
	Location during cognitive tests (1 item)	4× per day	
	Distractions during tests (4 items with branching logic)	4× per day	
	Substance use (1 item)	4× per day	
	Activity pacing (3 items)	3× per day^a^	
	Sleep quality (2 items)	Morning	
	Overnight falls (4 items with branching logic)	Morning	
	Social participation (6 items)	Evening	
	Physical function (2 items)	Evening	
	Daytime falls (4 items with branching logic)	Evening	

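### Aim 3's long-term comparison lets self-rated cognition count on the ambulatory side but names only test scores on the clinic side, so for self-reported outcomes it cannot separate setting from type of report

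*Protocol article*

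**What the plan says.** **Ambulatory predictors.** Aim 3 (Short Term) predicts same-day functioning "from the ambulatory cognitive variables". Aim 3 (Long Term) uses "the cognitive variables (averaged across each time period) predicting social and physical functioning at 1- and 2-year follow-up". Neither passage lists these variables. The article's definition is under Aim 2 (Short Term), where models are built "one for each ambulatory cognitive variable (perceived cognitive function and cognitive test scores"). Table 3 agrees: besides Symbol Search and Dot Memory, the app collects "Perceived cognitive function (3 items"), four times a day.

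**Clinic predictors.** The long-term models are to be "repeated in a set of secondary analyses with standard clinic-based cognitive test scores as predictor variables".

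**Comparison.** Prediction of long-term change "from ambulatory cognitive measures will be compared to the ability of laboratory-based measures to predict these same changes". The section expects the ambulatory measures to show stronger associations and gives greater reliability as the reason.

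**Outcomes.** The annual social outcome in Table 1 is the "Neuro-QoL Ability to Participate in Social Roles and Activities Short Form 8"; within the burst it is six evening self-report items (Table 3). Physical function has self-report scales (Neuro-QoL upper and lower extremity, Table 1) and performance tests (NIH Toolbox motor battery, Table 2). Each long-term model adjusts for the T1 value of its outcome.

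**Unused counterpart.** The visit battery contains a self-rating of cognition, "PROMIS Cognitive Abilities Short Form 8", which the Aim 3 text does not name as a clinic-side predictor.

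**The concern.** A comparison of ambulatory with laboratory prediction is informative about setting only if the two sides differ mainly in setting. Here they can also differ in type of report: the ambulatory side may contain the participant's own rating of cognition, and the stated clinic side holds performance scores only. When the outcome is also a self-report, a self-rated predictor shares rater, response style and current mood with it. A clinic test does not.

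The article already expects the ambulatory side to do better and attributes that to reliability. An advantage that came from self-rating would look the same and could be credited to reliability or to daily-life assessment. What is at stake is the reading of one secondary comparison, though that comparison bears on the study's central theme that ambulatory assessment improves on clinic testing.

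**Working it through.** **1. The two sides as written**

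| | Ambulatory side | Clinic side |
|---|---|---|
| Performance tests | Symbol Search, Dot Memory (Table 3) | Cognitive test scores (Aim 3, Long Term); 12 tests in Table 2 |
| Self-rated cognition | Perceived cognitive function, 3 items (Table 3; Aim 2 definition) | None named; PROMIS Cognitive Abilities is collected (Table 1) |

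| Outcome | Self-report | Performance |
|---|---|---|
| Social functioning | Neuro-QoL; six evening items | None |
| Physical functioning | Neuro-QoL extremity scales; evening items | NIH Toolbox motor battery; backward walk |

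The mismatch therefore touches every social outcome and part of physical function. Aim 2 (Long Term) names subjective and objective measures for both settings but rules out a direct comparison. Aim 3 makes the comparison without that symmetry.

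**2. Can shared reporting style alone favour the ambulatory side?**

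The article gives no figure for this comparison, so there is none to reproduce. Only N = 210 comes from the article (expected at final follow-up). All other values are assumptions:

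- true cognition unrelated to true social function;
- T1-T3 correlation 0.8 for cognition, 0.7 for social function, 0.6 for reporting style;
- reliability 0.80 for tests, the same in both settings, and 0.85 for self-reports;
- a share s of self-report variance due to reporting style, from 0 to 30%.

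Model: T3 self-reported outcome on its T1 value plus one cognitive predictor, two-sided 5% test, 3,000 simulated studies. The table is for predictors from the same period as the outcome (T3):

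| s | Self-rated cognition significant | Clinic test significant | Self-rated has larger partial R² |
|---|---|---|---|
| 0 | 5% | 5% | 48% |
| 10% | 20% | 5% | 71% |
| 20% | 65% | 5% | 90% |
| 30% | 94% | 5% | 98% |

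With T1 predictors, self-rated cognition is significant in about 5% of runs and has the larger partial R² in about 50%, at every s.

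**3. Algebra behind the simulation, at s = 0.2**

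With unit variances, the outcome's T1-T3 correlation is r_Y = 0.2×0.6 + 0.8×0.85×0.7 = 0.596.

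- T3 predictor: covariance 0.2 with the T3 outcome and 0.2×0.6 = 0.12 with the T1 outcome. Partial r = (0.2 − 0.12×0.596) / √[(1 − 0.12²)(1 − 0.596²)] = 0.1285/0.797 = 0.161, so partial R² = 0.026. Adding the chance level of about 1/208 = 0.005 gives 0.031, the simulated mean.
- T1 predictor: covariance 0.12 with the T3 outcome and 0.2 with the T1 outcome. The numerator is 0.12 − 0.2×0.596 = 0.0008, effectively zero.

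The T1 numerator is s × (stability of reporting style − r_Y). It vanishes here because 0.6 and 0.596 nearly coincide. If reporting style were as stable as cognition is assumed to be (0.8), r_Y = 0.16 + 0.476 = 0.636, the numerator is 0.2×0.164 = 0.0328, and partial r = 0.0328/√(0.96×0.5955) = 0.043, a partial R² of 0.002. So T1 adjustment removes or greatly reduces the artefact, depending on these stabilities.

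**4. Matched pairs under the same assumptions (s = 0.2, T3 predictor)**

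Mean partial R² is 0.005 for the app test and 0.005 for the clinic test. It is 0.031 for ambulatory self-rating and 0.031 for visit self-rating. Within each pair neither setting has an artificial advantage. The inflation on the self-report pair is still there, but equal on both sides.

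**The case against.** **The asymmetry is put together from two aims.** Aim 3 does not list its ambulatory variables, and its comparison sentence says laboratory-based measures. Elsewhere that label covers self-report: Aim 2 (Long Term) applies it to subjective measures, and Table 1 sits under the laboratory visit measures. PROMIS Cognitive Abilities could therefore be meant. This reading is possible, but the only clinic-side models the article states use test scores, so it does not remove the mismatch.

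**No joint ambulatory model is stated.** If variables are modelled one at a time, an app-test against clinic-test contrast is available. That is correct, but the article does not make that contrast the basis of its comparison.

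**T1 adjustment protects.** This largely stands where only T1 cognition is the predictor, and adjustment for personality may absorb some response style as well. However, the text averages cognition over each period and speaks of cognitive changes alongside changes in functioning, so same-period predictors are within the plan. Even with T1 predictors, a real predictive effect of self-rating would be attributed to setting.

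**Physical function is only partly exposed.** This stands: performance-based motor outcomes share no self-report with the predictors.

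**Stronger readings a reader might infer.** One is that the ambulatory side will win by several-fold, or in nearly all studies. That needs an assumption that perceived cognition is the stronger predictor, which presupposes the result, and it needs a single clinic test on the other side although Table 2 lists 12. Another is that the whole of Aim 3 is biased. The documents support neither.

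**Conclusion.** The point holds for the Aim 3 long-term secondary comparison, for social functioning and for the self-reported physical scales. As written, setting and type of report are mixed, and an ambulatory advantage on these outcomes could not be assigned to either.

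The size cannot be derived from the documents. The simulated percentages rest on assumed values and show only that the mechanism can operate with same-period predictors and is small or absent with T1-only predictors. The conclusion also depends on carrying Aim 2's definition of the ambulatory cognitive variables into Aim 3, which is the natural reading because Aim 3 uses the same term without restricting it.

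The comparison is secondary and no decision rule is attached to it, but the change should be made before analysis, which had not begun when the article was submitted.

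**What to change.** Base the ambulatory-versus-laboratory comparison in Aim 3 on two matched pairs, reported separately:

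- (a) Symbol Search and Dot Memory burst means against the clinic processing-speed and working-memory tests;
- (b) momentary perceived cognition against PROMIS Cognitive Abilities.

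State that perceived cognition, alone or within a set, will not be compared with clinic tests alone. For physical function, also run pair (a) on the performance-based NIH Toolbox motor outcomes.

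All these measures are already being collected. The cost is a change of wording, a few extra models, and two narrower comparisons in place of one broad claim.

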## Results

This research received funding on August 1, 2021, from the Eunice Kennedy Shriver National Institute of Child Health & Human Development (R01HD102337-01A1). Enrollment and T1 data collection occurred between May 12, 2022, and February 29, 2024. The study recruited 301 individuals with MS (UM: n=107, WSU: n=102, and UW: n=92); of these, 274 (UM: n=101, WSU: n=88, and UW: n=85) participated in T1 data collection. Longitudinal data collection will continue through March 2026. Data analysis has not yet started as of the time of this submission.

## Discussion

### Principal Findings

The anticipated findings of this study are 3-fold. First, we anticipate that ambulatory cognitive tests will be more sensitive to subtle cognitive changes in people with MS over 1-2 years. Second, we expect to identify modifiable factors (eg, mood, sleep, and physical activity) that precede and predict later cognitive decline on a short- and long-term scale. This information could help to prevent future decline or mitigate current cognitive dysfunction. Third, we hypothesize that cognitive changes will predict changes in social and physical function on a short- and long-term scale; such information will help to delineate the full impact of cognitive change in MS.

The collection of intensive longitudinal data in a large, heterogenous sample will allow for an in-depth characterization of individuals with MS and provide multiple avenues for future research. Data from this study are expected to inform comprehensive models of cognitive change in MS as well as provide insights on potential targets for intervention development to help people with MS optimize cognitive function.

### Strengths and Limitations

One limitation of this study is that the inclusion criteria require participants to be able to ambulate. The rationale for this criterion is that we would like to collect meaningful accelerometer data in order to explore the associations between physical activity and cognitive function. However, this criterion limits the generalizability of the findings to those with more significant mobility limitations.

This study has a number of notable strengths. Technology-enabled assessment of day-to-day cognitive function in the lived environment has the potential to greatly improve the sensitivity and ecological validity of cognitive assessment in people with MS. The advancement of measurement sensitivity is critical, as cognitive changes can be subtle and compound slowly over time; however, despite the small magnitude of these changes, individuals with MS often report distress over noticeable changes in their cognition that are not detected on standard laboratory-based cognitive tests. Another advantage is the intensive within-person design that allows for the exploration of dynamic associations between potentially modifiable predictors of cognitive dysfunction while accounting for “third variables” such as a person’s disease severity, age, and sex. AnΩΩΩhone. This allows for exploring different trajectories of change over time.

### Future Directions

Future work that capitalizes on the findings of this study and advances in assessment methods can also be used to improve treatment decision-making, including the timing and type of treatment approach. We will use these findings to design and test trials of behavioral, medical, and combination therapies to prevent cognitive decline and improve cognitive functioning in people with MS. Additionally, our innovative assessment methods may also be used to improve the measurement of outcomes in clinical trials of both pharmacological and nonpharmacological interventions, enriching understanding of the effects of such interventions. To our knowledge, there are few studies that track cognitive and other functional domains in MS beyond 2 years; thus, long-term outcomes will yield a rich dataset for understanding longitudinal function in persons with MS.

## Appendix

Multimedia Appendix 1 Detailed description of CogDetect-MS self-report measures. CogDetect-MS: Optimizing Detection and Prediction of Cognitive Function in Multiple Sclerosis.

Multimedia Appendix 2 Detailed description of CogDetect-MS performance-based measures. CogDetect-MS: Optimizing Detection and Prediction of Cognitive Function in Multiple Sclerosis.

Multimedia Appendix 3 Detailed description of CogDetect-MS ambulatory self-report measures. CogDetect-MS: Optimizing Detection and Prediction of Cognitive Function in Multiple Sclerosis.

## Abbreviations

CogDetect-MS: Optimizing Detection and Prediction of Cognitive Function in Multiple Sclerosis
EMA: ecological momentary assessment
HIPAA: Health Insurance Portability and Accountability Act
IRB: institutional review board
MLM: multilevel model
MS: multiple sclerosis
NIHTB: National Institutes of Health Toolbox
REDCap: Research Electronic Data Capture
UM: University of Michigan
UW: University of Washington
WSU: Wayne State University
